## Abstract

Delta-9-tetrahydrocannabinol (Δ^9^-THC) and other cannabinoids present in cannabis (marijuana) have been shown to affect the normal inhibitory pathways that influence nociception in humans. The potential benefits of cannabinoids as an analgesic are likely greatest in hyperalgesic and inflammatory states, suggesting a role as a therapeutic agent for treating acute pain following injury. Dronabinol is a licensed form of Δ^9^-THC. The primary objective of this single center randomized controlled trial is to evaluate the efficacy of adjunctive dronabinol versus control (systemic analgesics only, no dronabinol) for reducing opioid consumption in adults with traumatic injury. Study inclusion is based on high baseline utilization of opioids ≥50 morphine equivalents (mg) within 24 h of admission for adults aged 18–65 years with traumatic injury. There is a 48-hour screening period followed by a 48-hour treatment period after randomization. A total of 122 patients will be randomized 1:1 across 2 study arms: adjunctive dronabinol versus control (standard of care using systemic analgesics, no adjunctive dronabinol). Patients randomized to the dronabinol arm should receive their first dose within 12 h of randomization, with a dose range of 5 mg up to 30 mg daily in divided doses, in addition to systemic analgesics as needed for pain. The primary efficacy endpoint is a change in opioid consumption (morphine equivalents), assessed post-randomization (48 h after randomization) minus pre-randomization (24 h prior to randomization). This is the first randomized trial to investigate whether adjunctive dronabinol is effective in reducing opioid consumption in acute pain management of traumatic injury. Trial Registration: ClinicalTrials.gov Identifier: NCT03928015.

## 1. Introduction

Delta-9-tetrahydrocannabinol (Δ^9^-THC) and other cannabinoids present in cannabis (marijuana) have been shown to affect the normal inhibitory pathways that influence nociception in humans. Cannabinoids act through the binding of two cannabinoid receptors coupled through G proteins; CB1 receptors are predominantly found at central and peripheral nerve terminals, where they mediate transmitter release, while CB2 receptors are highly expressed throughout the immune system [1].

The evidence demonstrating a therapeutic effect of THC and cannabis-based medications is still emerging but is well established for treating chronic pain based on three influential peer-reviewed publications [2,3,4]. These publications also provide conclusive evidence for a therapeutic effect of cannabis-based medications as anti-emetics and for multiple sclerosis symptoms. There is moderate evidence for improving sleep outcomes associated with sleep apnea, fibromyalgia, multiple sclerosis, and chronic pain. There is insufficient or low-quality evidence in all remaining conditions that have been studied. For instance, there is a dearth of research on cannabinoid use for acute pain management. A 2017 systematic review identified seven randomized controlled trials (RCT) assessing the analgesic efficacy of cannabinoid medications for acute pain [5]. Of these studies, five RCTs demonstrated that cannabinoids were equivalent to placebo, in one RCT cannabinoids were superior to placebo, and in one RCT cannabinoids were inferior to placebo. These limited and inconsistent data justify the necessity to perform additional studies on the analgesic effects of cannabinoids for acutely painful conditions.

Patients commonly experience severe, acute pain following traumatic injury that is treated with analgesics, particularly opiates. The antinociceptive properties of cannabinoids may be greatest in hyperalgesic and inflammatory states, suggesting a therapeutic role for treating pain following injury [6]. Moreover, pre-clinical studies support a potential role of Δ^9^-THC and cannabinoids as an adjunctive agent to opioids in painful conditions, via synergistic enhancement of mu opioid antinociception as well as the prevention of tolerance to and withdrawal from opiates [7,8,9].

Recently published preliminary clinical research from our group examined the effect of adjunctive dronabinol for acute pain management among 66 trauma patients [10]. Cases demonstrated a significant reduction in opioid consumption (morphine equivalents) from baseline with adjunctive dronabinol (−79 mg, *p* < 0.001), while the change in opioid consumption for matched controls was unchanged from baseline (−9 mg, *p* = 0.63), resulting in a nine-fold greater reduction in opioid consumption for cases versus controls that was significantly different between pairs (difference: −70 mg, *p* = 0.02). There were no differences in secondary outcomes. These results suggest that adjunctive dronabinol used as part of a multimodal analgesia regimen may result in a marked reduction in opioid consumption

Two subset analyses of this matched cohort study provide mixed evidence that the opioid sparing effect of dronabinol may be greater in patients who are marijuana users. Among the subset of 19 cases who were marijuana users, opioid consumption was significantly reduced with adjunctive dronabinol (−97 mg, *p* < 0.001) versus no change in opioid consumption in 19 matched controls (1 mg, *p* = 0.70), with a difference between pairs that was significant: −108 mg, *p* = 0.01) [10]. However, when examining the subset of patients who received dronabinol, there were no differences in the change in opioid consumption for patients who were marijuana users (*n* = 21, −97 mg reduction with dronabinol) compared to non-marijuana users (*n* = 15, −64 mg reduction with dronabinol), *p* = 0.41 (unpublished). 

We are recruiting patients in a RCT to evaluate the efficacy of adjunctive dronabinol on opioid utilization for acute pain management. The primary trial objective is to evaluate the efficacy of adjunctive dronabinol versus control (systemic analgesics only, no dronabinol) for reduction in opioid consumption in adults with traumatic injury. Dronabinol is a licensed form of Δ^9^-THC. Dronabinol is not FDA approved for acute pain management; however, it has been in use at our level I trauma center system formulary without restriction since 2015. 

## 2. Materials and Methods

### 2.1. Study Design and Setting 

This is an open label RCT being performed at a single level I trauma center: St. Anthony Hospital in Lakewood, CO. This RCT was designed primarily to determine whether adjunctive dronabinol reduces opioid consumption compared to control. The study was designed with a stratified randomization by baseline marijuana use, which is intended to determine whether the treatment effect of dronabinol is greater in chronic marijuana users compared to recreational or non-marijuana users. This stratified randomization design was incorporated based on the gestalt that cannabis-based medication has a greater benefit for marijuana users.

There is a 48-hour screening/randomization window, a 48-hour treatment window, and a total participation period extending through the acute hospitalization. A description of the clinical trial is posted at ClinicalTrials.gov.

### 2.2. Study Subjects

Patients are being recruited from the participating trauma center to which they are acutely presenting. A total of 122 adult trauma patients will be randomized 1:1 across 2 study arms: adjunctive dronabinol or control (systemic analgesics only), as shown in Figure 1. 

Patients should fulfill all of the following inclusion criteria:Male or female, 18 years to 65 years old (inclusive).Diagnosis of traumatic injury based on ICD10 diagnosis of S00-T14, which covers injuries to any region of the body.Moderately high initial morphine equivalent use ≥50 mg within a 24-hour window during the screening period. Opioids will be converted to morphine equivalents (mg) using an Equianalgesic conversion chart, Table 1 [11].Willing to disclose current marijuana status (current user (habitual/chronic or recreational), former user, never user).

Patients fulfilling one or more of the following criteria may not be enrolled in the study:Patients on a pain management agreementPatients who are nil per os (NPO) at the time of randomization or are expected to be NPO within the next 48 h, with the exception for a brief NPO period for surgical proceduresPatients who have received or are expected to receive neuraxial/locoregional blocks for pain within the next 48 hoursPatients with a known allergy or previous hypersensitivity reaction to dronabinol or sesame oilPatients prescribed dronabinol between arrival and prior to randomizationPregnancy or breast feedingIncarceration (presumed; patients are not arraigned until after hospital discharge).

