### 2.3. Study Visits

The following procedures will be performed at screening, within 48 h of hospital admission: ensure patient meets inclusion and exclusion criteria; record 24-hour total morphine equivalents; record habitual marijuana usage; obtain informed consent via patient or proxy. 

Once patients are confirmed to meet all criteria and have signed an informed consent, they will be randomized 1:1 across the two study arms (dronabinol or control, Figure 1). The following procedures will be performed during randomization: randomize the patient using the Microsoft Excel blinded randomization schema; record pain using the patient self-reported pain numeric rating scale (NRS, 0–10 scale). 

The following procedures will be performed during the acute hospitalization, post-randomization: if randomized to the dronabinol arm, administer the first dose within the first scheduled dose window and within 12 h of randomization. Record all doses received, including date, time and dose; record all opioid and non-opioid systemic analgesics received, including route/dose/frequency; record all non-analgesic concomitant medications; record pain NRS scores at the following time points: once admitted in hospital bed, preoperatively in the OR prior to anesthesia, one hour post operatively; record all analgesic complications; record all documented drug use from patient self-report and urine drug screening results. Detailed information on the regularity of marijuana use will also be recorded. 

The following procedures will be performed at hospital discharge: record discharge pain NRS score; record discharge location; re-consent, if necessary. 

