### 2.7. Statistics

Significance is set at an alpha value of 0.05. SAS (Cary, NC) software will be used for statistical analysis. All efficacy analyses will be performed in the intent-to-treat population, defined as all patients who are randomized. Subset analyses will be performed by habitual marijuana use. 

The primary endpoint is the change in morphine equivalents and will be assessed as: post-randomization (48 h after randomization) minus pre-randomization (24 h prior to randomization). No imputation will occur for the primary endpoint. The change in morphine equivalents (mg) will be analyzed with an analysis of covariance (ANCOVA) model to examine the effect of treatment arm, adjusted for age, gender, injury severity score, and clinical characteristics that differ between groups with *p* < 0.15. Of note, our study inclusion criteria allow for patients to present with polytrauma. We anticipate the majority of patients will have injuries to the thorax and extremities, with few patients presenting with severe TBI because administration of opioids and other drugs that alter a neurological assessment tend to be used sparingly. Should there be differences in injury patterns, despite the 1:1 randomization procedure, these differences will be adjusted for in the primary ANCOVA analysis.

Secondary efficacy analyses include the difference between treatment groups in: hospital disposition, hospital complications, and analgesic complications, reported as proportion (%) and analyzed with chi-square tests; morphine equivalents over the hospitalization, hospital length of stay (days), time (h) to transition to non-opioid analgesia, pain NRS scores at all specified time points, reported as median (IQR) and analyzed with a Wilcoxon rank-sum test. Analgesic complications will be described by severity as mild, moderate and severe.

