### 2.8. Sample Size

The planned enrollment is 122 patients total randomized 1:1 across two study arms: dronabinol or no dronabinol (systemic analgesia only). The sample size is based on a 38% reduction in morphine equivalents with adjunctive dronabinol vs. an 8% reduction in morphine equivalents for systemic analgesics only, with a pooled standard deviation of 58. The analysis was performed using two sample mean tests with normal approximation and equal weights. These estimates were derived via bootstrapping of the final matched study sample of 66 patients. The power to demonstrate the main effect of dronabinol over systemic analgesics is 80% using a 2-tailed alpha of 0.05. 

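### The 50 mg entry criterion is stated over two different windows, neither tied to the 24 h baseline of the primary endpoint

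*Protocol article*

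**What the plan says.** The protocol article defines three windows for opioid use before treatment.

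- **Entry, Abstract:** "Study inclusion is based on high baseline utilization of opioids ≥50 morphine equivalents (mg) within 24 h of admission".
- **Entry, section 2.2:** "Moderately high initial morphine equivalent use ≥50 mg within a 24-hour window during the screening period". Section 2.1 gives the length of that period: "There is a 48-hour screening/randomization window, a 48-hour treatment window". Section 2.3 anchors it to admission: "The following procedures will be performed at screening, within 48 h of hospital admission".
- **Baseline of the primary endpoint, section 2.7 (the Abstract agrees):** the change is "post-randomization (48 h after randomization) minus pre-randomization (24 h prior to randomization").

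Section 2.3 also has staff "record 24-hour total morphine equivalents" at screening, without saying when those 24 h start or end. No section requires the qualifying window to be the baseline window.

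The covariates named for the ANCOVA in section 2.7 are age, gender and injury severity score, plus clinical characteristics that differ between arms at p < 0.15. Pre-randomization opioid use is not among the named ones.

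**The concern.** Eligibility and the endpoint baseline are both fixed in this document, so this is not a detail left to an analysis plan. Two statements of one entry rule conflict, and staff applying one will enrol patients whom the other excludes. The Abstract also uses the word baseline for the qualifying amount, although the endpoint's baseline is another window.

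The endpoint is an absolute change in mg, and use cannot fall below zero. A threshold on opioid use helps to secure room for a fall only if it applies to the period from which the change is measured. If qualifying use has already dropped by the time of randomization, the patient contributes a small baseline and a small possible reduction.

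**Working it through.** **The plan's own figure.** Section 2.8 rests on this: "The sample size is based on a 38% reduction in morphine equivalents with adjunctive dronabinol vs. an 8% reduction in morphine equivalents for systemic analgesics", with SD 58, two-sided alpha 0.05 and 80% power. Taking the difference of 30 and the SD of 58 in the same unit (the section gives none for the SD), n per arm = 2 × (1.960 + 0.842)² × 58² / 30² = 58.7, so 59 per arm or 118 in total. The t-test version gives 60 per arm, 120 in total. With 61 per arm the power is 81.5%. The stated 122 is thus close to what the inputs give, and nothing below changes it.

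**Do the two entry rules differ?** Count hours from admission. The first 24 h are one of the possible 24 h windows in a 48 h screening period, so anyone who meets the Abstract rule also meets the section 2.2 rule. The reverse fails: a patient with 20 mg in hours 0–24 and 60 mg in hours 24–48 passes section 2.2 and fails the Abstract. Section 2.2 is the wider rule.

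**Does qualifying use fall inside the baseline?** For randomization at hour t, the baseline is [t − 24, t]. Its overlap with the first 24 h is min(t, 24) − max(t − 24, 0).

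| Randomized at (h) | In-hospital hours in baseline | Overlap with hours 0–24 |
|---|---|---|
| 12 | 12 | 12 |
| 24 | 24 | 24 |
| 30 | 24 | 18 |
| 36 | 24 | 12 |
| 42 | 24 | 6 |
| 48 | 24 | 0 |

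- **t ≤ 24:** all in-hospital use before randomization lies inside the baseline window. Whatever use met the criterion is in the baseline, so the baseline is at least 50 mg. For t < 24 it covers fewer than 24 h in hospital.
- **24 < t ≤ 48:** part of the qualifying use can fall outside. Take 60 mg spread evenly over hours 0–24 and 24 mg spread evenly over hours 24–48. At t = 36 the baseline is 30 + 12 = 42 mg; at t = 48 it is 24 mg. Section 2.2 accepts any 24 h window, so the same can happen under it.

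**How often?** The documents give neither randomization times nor a distribution of daily use, so this is illustration only. Assumed: log-normal day-1 use with median 70–140 mg and log-SD 0.6, day-to-day log-SD 0.35, and even use within each day. Share of day-1 qualifiers with a baseline below 50 mg:

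| Randomized at (h) | Day 2 at 80% of day 1 | Day 2 at 60% of day 1 |
|---|---|---|
| 24 | 0% | 0% |
| 36 | 2.6–10.4% | 5.0–18.8% |
| 48 | 8.9–24.3% | 19.4–44.5% |

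With no average decline, the 48 h share is 4–12%. A different assumed model (day-1 mean 80 mg, coefficient of variation 0.7, day-to-day log correlation 0.5–0.7, day-2 mean 60–100% of day 1) gives 17–51% at 48 h.

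The assumed medians may be too low. If the mg changes in the Introduction and the percentages in section 2.8 describe the same data, the preliminary baselines were about 9 / 0.08 = 113 mg and 79 / 0.38 = 208 mg. At a median of 200 mg the 48 h shares drop to 3.8% and 9.5%. Against that, the Discussion concedes that opioid use may now be lower in both arms.

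**Effect on the absolute difference.** If the planned percentages held at every baseline, the difference between arms would be (0.38 − 0.08) × baseline: 30 mg at a baseline of 100 mg and 12 mg at 40 mg.

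**The case against.** The Abstract could be read as shorthand, and section 2.2 does speak of initial use, which hints at the first day. That eases the conflict but does not remove it, because section 2.2 still accepts any 24 h window in the screening period. No section says that the criterion is meant to guarantee a minimum endpoint baseline; that purpose is inferred.

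Several objections to a stronger reading stand:

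- **Short stays.** A reader might infer that a truncated baseline also produces values below 50 mg. It does not: with randomization at or before 24 h, all qualifying use is in the baseline.
- **Frequency.** A reader might take the 48 h shares as expected rates. They are the extreme case on assumed inputs, and nothing indicates that randomization at 48 h is typical.
- **The 70 mg difference in the preliminary study.** It is tempting to say that a patient with a baseline below 50 mg cannot show such a fall. The trial is planned on percentage reductions, and a 38% fall is possible from any baseline above zero.
- **Noise.** A floor compresses change scores. Whether low baselines raise or lower the SD cannot be shown from the documents.
- **Identical windows.** Qualifying on one measurement and taking baseline from another is a recognised way to limit regression to the mean. Selecting on the same 24 h that serves as baseline inflates the apparent within-arm fall in both arms. Requiring identical windows is therefore partly a design preference.

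**Conclusion.** The point holds as a contradiction in the eligibility rule and an unstated link between the qualifying window and the endpoint baseline. Both follow directly from the text. Low baselines can arise only with randomization between 24 and 48 h after admission, and only when use has fallen below 50 mg per 24 h by then. How often that happens, and what power it costs, cannot be computed from the documents; the percentages above rest wholly on assumed inputs.

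A reader might infer that the mismatch biases the treatment comparison. The documents do not support that. It arises before randomization and affects both arms alike, so its consequence is ambiguous eligibility and possible dilution of the absolute effect. Severity is minor to moderate.

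**What to change.** 1. Reconcile the Abstract and section 2.2 to one entry window, and state how it relates to the endpoint baseline. Using the 24 h ending at randomization for both is one option. It needs a rolling 24 h total at randomization, changes eligibility in a trial that is already recruiting, slows recruitment slightly, and brings the regression to the mean noted above.
2. When a patient has been in hospital for less than 24 h at randomization, express baseline as mg per 24 h observed (total × 24 / hours observed). This costs one line of text, but scaling magnifies short records: 50 mg by hour 10 becomes 120 mg per 24 h.
3. Name pre-randomization 24 h morphine equivalents as a prespecified ANCOVA covariate, rather than leaving it to the p < 0.15 rule. The data are already needed for the endpoint, so there is no collection cost.
4. Add a sensitivity analysis restricted to patients whose pre-randomization baseline was at least 50 mg. The restriction uses only information from before randomization, so the randomized comparison is kept within the subset, and it covers patients already enrolled. The price is a smaller sample in that analysis.

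The planned total of 122 need not change.

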### 2.3. Study Visits

The following procedures will be performed at screening, within 48 h of hospital admission: ensure patient meets inclusion and exclusion criteria; record 24-hour total morphine equivalents; record habitual marijuana usage; obtain informed consent via patient or proxy. 

Once patients are confirmed to meet all criteria and have signed an informed consent, they will be randomized 1:1 across the two study arms (dronabinol or control, Figure 1). The following procedures will be performed during randomization: randomize the patient using the Microsoft Excel blinded randomization schema; record pain using the patient self-reported pain numeric rating scale (NRS, 0–10 scale). 

The following procedures will be performed during the acute hospitalization, post-randomization: if randomized to the dronabinol arm, administer the first dose within the first scheduled dose window and within 12 h of randomization. Record all doses received, including date, time and dose; record all opioid and non-opioid systemic analgesics received, including route/dose/frequency; record all non-analgesic concomitant medications; record pain NRS scores at the following time points: once admitted in hospital bed, preoperatively in the OR prior to anesthesia, one hour post operatively; record all analgesic complications; record all documented drug use from patient self-report and urine drug screening results. Detailed information on the regularity of marijuana use will also be recorded. 

The following procedures will be performed at hospital discharge: record discharge pain NRS score; record discharge location; re-consent, if necessary. 

### 2.4. Randomization and Blinding

Patients will be assigned to treatment by a randomization schedule developed and maintained by an independent statistician. The randomization allocation sequence was computer generated and is blinded, with allocation hidden until a patient has met all inclusion and exclusion criteria and provided informed consent. Randomization will occur in a 1:1 fashion in blocks of 2 and 4 and stratified by habitual marijuana user (yes/no). 

The assessor, participants, treatment team, and statisticians are unblinded. All assessments are standard and routinely collected by the assessors (ICU and general ward nursing staff), including pain NRS scores and analgesia administration. 

